#### Secondary Outcomes

The secondary outcomes are the mean differences in the FFMQ, UWES-9, SWLS, FS, SPANE, EQ, PSS, ICECAP-A, TPS, and SEC scores at 4 weeks, 3 months, and 6 months postintervention.

### Evaluation of Health Economics

Cost-effectiveness was measured by calculating the incremental cost-effectiveness ratio, which is the incremental cost divided by the incremental effectiveness between the groups. Incremental effectiveness was evaluated using quality-adjusted life-years, calculated from the weighted ICECAP-A scores. The analyses were conducted from a company’s perspective (ie, direct cost). Cost benefit will be evaluated using the net monetary benefit, which is calculated by subtracting the incremental cost needed for the intervention from the net monetary benefit of incremental productivity, weighted by the WHO-HPQ score.

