### Baseline Assessment

The included participants completed the questionnaires administered for the collection of demographic and psychosocial data. The psychological assessment tools to be utilized include the WHO-HPQ, the Five Facet Mindfulness Questionnaire (FFMQ), the 9-item Utrecht Work Engagement Scale (UWES-9), the Satisfaction With Life Scale (SWLS), the Flourishing Scale (FS), the Scale of Positive and Negative Experience (SPANE), the Experiences Questionnaire (EQ), the Perceived Stress Scale (PSS), the Investigating Choice Experiments Capability Measure for Adults (ICECAP-A), Team Psychological Safety (TPS), and the Credibility/Expectancy Questionnaire (CEQ). The details of each scale are presented later in the Instruments section.

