#### Investigating Choice Experiments Capability Measure for Adults

ICECAP-A was developed to measure capability well-being in adults, which the existing health-related quality-of-life scales have not been able to adequately capture. It is a scale of 5 attributes, each with 4 levels. It provides a single index value for well-being utility, either 0 or 1. A higher score indicates better well-being status [54].

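### The cost-effectiveness ratio is stated per QALY, but its effect measure comes from ICECAP-A, which the protocol describes as a capability well-being index, so the unit is mislabelled

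*Protocol article*

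**What the plan says.** In the protocol article, Evaluation of Health Economics, the incremental cost-effectiveness ratio is "the incremental cost divided by the incremental effectiveness between the groups". The effect unit is then fixed: "Incremental effectiveness was evaluated using quality-adjusted life-years, calculated from the weighted ICECAP-A scores". The perspective is that of the company, with costs limited to direct cost.

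The Instruments section describes the source of that effect measure in these terms: "ICECAP-A was developed to measure capability well-being in adults, which the existing health-related quality-of-life scales have not been able to adequately capture". On the scale it adds: "It provides a single index value for well-being utility, either 0 or 1". The last phrase presumably means a range from 0 to 1. The section says that higher is better, but it does not say what state 0 or 1 represents, and it mentions neither death nor full health.

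The same health-economics section defines a second result, the net monetary benefit, as obtained by "subtracting the incremental cost needed for the intervention from the net monetary benefit of incremental productivity, weighted by the WHO-HPQ score".

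**The concern.** A QALY weights time by a health utility, conventionally anchored at dead = 0 and full health = 1. The protocol sets ICECAP-A apart from health-related quality-of-life scales in one section, then gives its time-weighted score a health-related quality-of-life unit in another. If the plan is followed as written, the trial will publish a cost per QALY whose denominator contains no health utility.

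Cost-effectiveness is named in the Objective and in the Aim, and this ratio is the only cost-effectiveness measure that the article defines. A reader who sees a per-QALY figure will take it to be on the same footing as other per-QALY figures, and here it would not be. The primary outcome, absolute presenteeism, is unaffected.

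The net monetary benefit sentence raises a smaller matter of wording: the term being defined reappears as an input to its own definition.

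**Working it through.** The article gives no numerical economic result, so there is no figure to reproduce. The check compares sections and adds two short illustrations.

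**1. Could another instrument supply a health utility?**
- Baseline Assessment and Tables 2 and 3 list WHO-HPQ, FFMQ, UWES-9, SWLS, FS, SPANE, EQ, PSS, ICECAP-A, TPS and CEQ. The tables add health service use and homework engagement.
- EQ here is the Experiences Questionnaire, a 20-item decentering scale, and not a health-utility measure.
- ICECAP-A is the only listed instrument described as yielding a utility index, and that index is of well-being.
- No mapping from ICECAP-A to a health-utility scale is mentioned.

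**2. What the described calculation produces.** Assume the usual area-under-the-curve method.
- Effect = (difference in index) × (time in years).
- Horizon: 28 weeks, from the Abstract's Methods.
- Assumed difference, held throughout (the article gives none): 0.02 to 0.05.
- 0.02 × 28/52 = 0.011 index-years.
- 0.05 × 28/52 = 0.027 index-years.

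The unit is that of the index, which is capability-weighted years.

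**3. How far this could be from QALYs.** Index-years equal QALYs only if the index and the QALY scale share both end points. Suppose, favourably, that the two scales are linearly related, that index 1 equals QALY weight 1, and that index 0 equals QALY weight h. Then
- QALY gain = (1 − h) × index-years
- true cost per QALY = reported ratio ÷ (1 − h)

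The article gives no value for h. Over an assumed range, with the 0.05 illustration (0.0269 index-years):

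| h (assumed) | QALY gain | True cost per QALY ÷ reported ratio |
|---|---|---|
| −0.2 | 0.0323 | 0.83 |
| 0 | 0.0269 | 1.00 |
| 0.2 | 0.0215 | 1.25 |
| 0.4 | 0.0162 | 1.67 |

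This range shows sensitivity to an unstated anchor and is not an estimate of error. If the two constructs are not linearly related, no single factor converts one to the other.

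**4. The net monetary benefit sentence.** Let B be the monetary value of the productivity gain and C the incremental cost.
- Natural reading: B − C.
- Reading in which the inner term is already net of C: (B − C) − C = B − 2C.
- With assumed B = 100 and C = 30: 70 against 40. With C = 60: 40 against −20.

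The readings differ by exactly C, and the sign reverses when B/2 < C < B. The difference arises only if the inner word net means net of programme cost, which the sentence does not say.

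**The case against.** The strongest defence of the QALY label has four parts.

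- The Instruments section does not say that ICECAP-A excludes health. Its wording also fits a broader construct of which health is a part, and it calls the output a utility.
- The scores are described as weighted, so some valuation is planned. The details of a value set could sit in a full protocol or an economic analysis plan that is not shown.
- The dead-to-full-health anchoring of a QALY is general methodology and is not stated in the article.
- Health economics is a secondary outcome, and the suggested correction leaves every number as it was.

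The last part stands and limits the severity. The others do not rescue the label. A broader construct is still not a health utility. The natural meaning of weighting is to apply the index's own values, which returns the well-being index that the Instruments section describes. The point is also not about missing detail: the article commits to a named unit that conflicts with its own description of the instrument.

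Two stronger readings are tempting, and the article supports neither. A reader might infer that programme cost is subtracted twice in the net monetary benefit. The sentence names two separate items, the intervention cost and a productivity benefit weighted by the WHO-HPQ score, and nothing says that the cost has already been taken out of the second. A reader might also infer that the ratio will be judged against a QALY threshold. The article names no threshold and no willingness-to-pay value, so such a comparison is a foreseeable misuse by others and not a planned step.

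**Conclusion.** The effect unit is wrong as written. The plan would produce a cost per capability-weighted year and call it a cost per QALY. The mislabelling affects the whole ratio, since the unit applies to its entire denominator, but the arithmetic does not change. Under the assumed anchors above, the true cost per QALY would be 0.83 to 1.67 times the reported figure. The article offers no basis for choosing a value in that range, or for the linear relation behind it.

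The conclusion rests on the conventional meaning of a QALY, on reading the weighted scores as the ICECAP-A index, and on the absence of any other utility source in the listed assessments. It does not extend to calling the whole economic evaluation invalid. The net monetary benefit is circularly worded, and its natural reading is the ordinary value minus cost.

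This should be corrected before the economic results are reported. It does not touch the primary analysis.

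**What to change.** In Evaluation of Health Economics:

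- Name the effect measure years of full capability, defined as the area under the ICECAP-A index over follow-up.
- Report the ratio as cost per year of full capability, and do not present it as cost per QALY.
- In the net monetary benefit definition, replace the inner term with monetary value of incremental productivity, so that the formula is plainly B − C with cost deducted once.

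These are wording changes. They use the same data, visits, sample size and computation. The one downside is that the ratio loses its apparent comparability with the cost-per-QALY literature, a comparability that the listed instruments do not support.

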#### Multivariable Analysis

To investigate factors that predict or mediate clinical outcomes, multivariate analysis will be conducted using factors obtained during the study. The details of the analytical methodology will be presented separately.

### Instruments

#### World Health Organization Health and Work Performance Questionnaire

The WHO-HPQ is a self-report instrument designed to estimate the workplace costs of health problems in terms of self-reported sickness absences and reduced job performance (presenteeism). Presenteeism is assessed using the following questions: “On a scale of 0-10, where 0 is the worst job performance anyone could have at your job and 10 is the performance of a top worker, how would you rate the usual performance of most workers in a job similar to yours?” and “Using the same 0-10 scale, how would you rate your overall job performance on the days you worked during the past 4 weeks?” A low presenteeism score indicates poor performance [46].

#### Five Facet Mindfulness Questionnaire

This tool is a self-report questionnaire used to assess dispositional mindfulness. It includes 5 factors, which are extracted based on a factor analysis of 5 mindfulness questionnaires developed independently. The 5 facets are observing, describing, acting with awareness, not judging one’s inner experience, and not reacting to one’s inner experience. Total scores range from 39 to 195. Higher scores indicate greater levels of dispositional mindfulness [47].

#### The 9-Item Utrecht Work Engagement Scale

The UWES-9 is a 9-item self-report questionnaire that is widely used to measure work engagement across countries. It is hypothesized to assess 3 aspects of work engagement: vigor, dedication, and absorption. Each aspect includes 3 items. The scores range from 0 to 54. Higher scores indicate higher work engagement [48].

#### Satisfaction With Life Scale

This is a 5-item self-report questionnaire used to evaluate the cognitive aspects of subjective well-being. Scores for each subscale range from 1 (*strongly disagree*) to 7 (*strongly agree*). Total scores range from 5 to 35, with higher scores indicating higher satisfaction [49].

#### Flourishing Scale

This scale includes 8 items relevant to significant aspects of human functioning, ranging from positive relationships to feelings of competence, meaning, and purpose in life. Responses to each item are rated on a scale of 1-7, ranging from *strong disagreement* to *strong agreement*. Possible total scores range from 8 (*strong disagreement* with all items) to 56 (*strong agreement* with all items). High scores indicate that respondents view themselves positively in important areas of functioning [50].

#### Scale of Positive and Negative Experience

This measure is a 12-item scale that assesses positive experiences (6 items) and negative experiences (6 items). Owing to the generality of the items included in this scale, it can assess pleasant and unpleasant feelings that are the focus of most scales and can also reflect other conditions, such as interest, flow, positive engagement, and physical pleasure. Positive (SPANE-P) and negative (SPANE-N) scale scores range from 6 to 30. Higher scores indicate a higher positive or negative affective status. Subtraction of the negative score from the positive score yields the SPANE-B score, which is between −24 and 24 [50].

#### Experiences Questionnaire

The EQ is a 20-item self-report measure based on a 5-point Likert scale that ranges from 1 (*never*) to 5 (*always*). The total score ranges from 20 to 100. The scale focuses on decentering, defined as the ability to view the self as separate and different from its own thoughts, the capacity for nonreacting to negative experiences, and the ability to be self-compassionate. The EQ has been found to be reliable, and convergent and discriminant validities have been established for both general and clinical samples. The EQ is also internally consistent, with temporal stability over a 1-month period and good convergent validity [51,52].

#### Perceived Stress Scale

The PSS was developed to assess the degree to which situations in one’s life are appraised as stressful. The scale has 2 versions: the 14-item version (PSS-14) and the 10-item version (PSS-10), which is similar to the 14-item version but with 4 items removed. We used the PSS-10 in this study. This scale is used to assess perceived stressful experiences or stress responses in the previous month. Each item is rated on a 5-point Likert scale ranging from 4 (*never*) to 0 (*very often*) to identify positive experiences or responses. Total scores range from 0 to 40. Higher scores indicate higher stress levels [53].

#### Investigating Choice Experiments Capability Measure for Adults

ICECAP-A was developed to measure capability well-being in adults, which the existing health-related quality-of-life scales have not been able to adequately capture. It is a scale of 5 attributes, each with 4 levels. It provides a single index value for well-being utility, either 0 or 1. A higher score indicates better well-being status [54].

#### Team Psychological Safety

The TPS is a scale developed for the assessment of a shared belief held by members of a team that the team is safe for interpersonal risk taking. This is a 8-item tool with a 7-point Likert scale. A higher score indicates that the respondent feels better psychological safety in the team [55].

#### Credibility/Expectancy Questionnaire

The CEQ is a quick and easy-to-administer scale used to measure treatment expectancy and rationale credibility in clinical trials. It consists of 6 items rated on a 9-point Likert scale, with 1 being *not at all* and 9 indicating *very logical/useful/confident/much*. Total scores range from 9 to 54. Higher scores represent higher credibility and expectancy for treatment. This scale is derived from 2 predicted factors: cognitive credibility and relatively more affective expectancy. These 2 factors are confirmed to be stable across different populations [56].

### Homework Engagement/Qualitative Data

Daily formal meditation time and the answers to open-ended questions are collected at the end of each session. The questions include the following: (1) What did you notice in this session? (2) Did you experience any difficulties in this session? (3) Do you have any comments to improve the sessions?

The validity and reliability of the original versions of all these scales have been confirmed [46-56]. Regarding the Japanese versions of the scales, the validity and reliability of all scales and questionnaires, except ICECAP, the TPS, and the CEQ, have been confirmed [57-62]. For ICECAP-A, the Japanese version of the ICECAP officially accepted by the University of Birmingham was used [63]. We adopted the Japanese version of the CEQ, which was translated by Ito et al [64] through a rigorous back-translation procedure with the permission and support of the original developer of the questionnaire. Regarding the TPS, we used the TPS questionnaire cited in the Japanese edition of *The Fearless Organization: Creating Psychological Safety in the Workplace for Learning, Innovation, and Growth* by Edmondson [65].

### Schedule for Assessments

In addition to the baseline assessment, we requested that the participants respond to these self-report assessments at 4 weeks, 3 months, and 6 months postintervention. A range of ±2 weeks from the scheduled dates for the baseline and postintervention assessments and ±4 weeks for the 3- and 6-month postintervention assessments were allowed. All assessment data were collected using the electronic patient-reported outcomes (ePRO) system. The assessment schedules are presented in Tables 2 and 3.

**Table 2 table2:** Assessment schedule for all participants.

Process/assessment	Screening period	Intervention period					Follow-up period						
		Week 1	Week 2	Week 3	Week 4	1 month		2 months	3 months	4 months	5 months	6 months	
Screening	A^a^	N/A^b^	N/A	N/A	N/A	N/A		N/A	N/A	N/A	N/A	N/A	
Informed consent	A	N/A	N/A	N/A	N/A	N/A		N/A	N/A	N/A	N/A	N/A	
bMBCT^c^	N/A	I^d^	I	I	I	F^e^		F	F	F	F	F	
Waitlist	N/A	N/A	N/A	N/A	N/A	N/A		N/A	N/A	N/A	N/A	N/A	
WHO-HPQ^f^	A	N/A	N/A	N/A	A	N/A		N/A	A	N/A	N/A	A	
FFMQ^g^	A	N/A	N/A	N/A	A	N/A		N/A	A	N/A	N/A	A	
UWES-9^h^	A	N/A	N/A	N/A	A	N/A		N/A	A	N/A	N/A	A	
SWLS^i^	A	N/A	N/A	N/A	A	N/A		N/A	A	N/A	N/A	A	
FS^j^	A	N/A	N/A	N/A	A	N/A		N/A	A	N/A	N/A	A	
SPANE^k^	A	N/A	N/A	N/A	A	N/A		N/A	A	N/A	N/A	A	
EQ^l^	A	N/A	N/A	N/A	A	N/A		N/A	A	N/A	N/A	A	
PSS^m^	A	N/A	N/A	N/A	A	N/A		N/A	A	N/A	N/A	A	
ICECAP-A^n^	A	N/A	N/A	N/A	A	N/A		N/A	A	N/A	N/A	A	
TPS^o^	A	N/A	N/A	N/A	A	N/A		N/A	A	N/A	N/A	A	
CEQ^p^	A	N/A	N/A	N/A	A	N/A		N/A	A	N/A	N/A	A	
Health service use	A	N/A	N/A	N/A	A	N/A		N/A	A	N/A	N/A	A	
Homework engagement/qualitative data	N/A	A	A	A	A	A		A	A	A	A	A	

^a^A: assessment.

^b^N/A: not applicable.

^c^bMBCT: brief mindfulness-based cognitive therapy.

^d^I: intervention.

^e^F: follow-up.

^f^WHO-HPQ: World Health Organization Health and Work Performance Questionnaire.

^g^FFMQ: Five Facet Mindfulness Questionnaire.

^h^UWES-9: 9-item Utrecht Work Engagement Scale.

^i^SWLS: Satisfaction With Life Scale.

^j^FS: Flourishing Scale.

^k^SPANE: Scale of Positive and Negative Experience.

^l^EQ: Experiences Questionnaire.

^m^PSS: Perceived Stress Scale.

^n^ICECAP-A: Investigating Choice Experiments Capability Measure for Adults.

^o^TPS: Team Psychological Safety.

^p^CEQ: Credibility/Expectancy Questionnaire.

**Table 3 table3:** Assessment schedule for participants in the waitlist control group, followed by a waiting period.

Process/assessment	Intervention period (followed by a waiting period)					Follow-up period (followed by a waiting period)					
	Week 1	Week 2	Week 3	Week 4	1 month		2 months	3 months	4 months	5 months	6 months
Screening	N/A^a^	N/A	N/A	N/A	N/A		N/A	N/A	N/A	N/A	N/A
Informed consent	N/A	N/A	N/A	N/A	N/A		N/A	N/A	N/A	N/A	N/A
bMBCT^b^	N/A	N/A	N/A	N/A	N/A		N/A	N/A	N/A	N/A	N/A
Waitlist	I^c^	I	I	I	N/A		N/A	N/A	N/A	N/A	N/A
WHO-HPQ^d^	N/A	N/A	N/A	A^e^	N/A		N/A	A	N/A	N/A	A
FFMQ^f^	N/A	N/A	N/A	A	N/A		N/A	A	N/A	N/A	A
UWES-9^g^	N/A	N/A	N/A	A	N/A		N/A	A	N/A	N/A	A
SWLS^h^	N/A	N/A	N/A	A	N/A		N/A	A	N/A	N/A	A
FS^i^	N/A	N/A	N/A	A	N/A		N/A	A	N/A	N/A	A
SPANE^j^	N/A	N/A	N/A	A	N/A		N/A	A	N/A	N/A	A
EQ^k^	N/A	N/A	N/A	A	N/A		N/A	A	N/A	N/A	A
PSS^l^	N/A	N/A	N/A	A	N/A		N/A	A	N/A	N/A	A
ICECAP-A^m^	N/A	N/A	N/A	A	N/A		N/A	A	N/A	N/A	A
TPS^n^	N/A	N/A	N/A	A	N/A		N/A	A	N/A	N/A	A
CEQ^o^	N/A	N/A	N/A	A	N/A		N/A	A	N/A	N/A	A
Health service use	N/A	N/A	N/A	A	N/A		N/A	A	N/A	N/A	A
Homework engagement	A	A	A	A	A		A	A	A	A	A

^a^N/A: not applicable.

^b^bMBCT: brief mindfulness-based cognitive therapy.

^c^I: intervention.

^d^WHO-HPQ: World Health Organization Health and Work Performance Questionnaire.

^e^A: assessment.

^f^FFMQ: Five Facet Mindfulness Questionnaire.

^g^UWES-9: 9-item Utrecht Work Engagement Scale.

^h^SWLS: Satisfaction With Life Scale.

^i^FS: Flourishing Scale.

^j^SPANE: Scale of Positive and Negative Experience.

^k^EQ: Experiences Questionnaire.

^l^PSS: Perceived Stress Scale.

^m^ICECAP-A: Investigating Choice Experiments Capability Measure for Adults.

^n^TPS: Team Psychological Safety.

^o^CEQ: Credibility/Expectancy Questionnaire.

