**Methods:**

We will conduct a 4-week randomized controlled trial (RCT) with a 6-month follow-up. Employees are included in the study if they (1) are between the ages of 20 and 65 years and (2) work longer than 30 hours weekly. Employees are randomly allocated to either the bMBCT group or the waitlist control group. The primary outcome of the study is the mean difference of productivity measured by the World Health Organization Health and Work Performance Questionnaire (WHO-HPQ) between the groups at 4, 16, and 28 weeks. Secondary outcomes include several clinical outcomes and health economics evaluation.

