### Interventions

#### Brief Mindfulness-Based Cognitive Therapy

The included participants were offered a bMBCT program, which is a modified version of the original MBCT developed by Segal et al [45]. The modifications followed Crane et al’s [1] specifications of “warp” (essential ingredients) and “weft” (flexible ingredients) of MBPs. To retain the essential ingredients of MBPs, we included practicing all mindful meditations except mindful movement and walking meditation (provided as homework via a delivery instruction movie). In contrast, considering the difference in the delivery setting (clinical setting vs workplace) and the target population (ie, patients with depression vs healthy individuals), some modifications were made. The first is the structure of the program. With the aim of improving accessibility to the program in the workplace, the duration of each session was shortened (from 2 hours to 1.5 hours), except session 1, and the total number of sessions was reduced (from 8 sessions to 4 sessions). To reflect the difference in the target population, the lecture relevant to depression was deleted, and activity records (ie, pleasant, unpleasant, appreciation events, and nourishing and depriving activities) were introduced to enhance the improvement of participants’ well-being. The specific program contents are listed in Table 1. In the program, participants learned both cognitive approaches and mindfulness practices (eg, raisin exercise, body scan, sitting meditation, exploring difficulty, and 3-step breathing space). The participants were asked to practice meditation daily for approximately 20 minutes by listening to the pre-recorded meditation guide audios and record some activities as homework (theme depends on the session). Monthly follow-up sessions (lasts for 1 hour) will be provided to the participants for 6 months. No regular homework will be assigned during the follow-up period. During the follow-up period, the participants can access the mindfulness website developed by the research team from a smartphone or a personal computer (PC) and easily stream/download the meditation instructions.

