### Control Group

Participants in the control group will wait until the intervention group has completed the intervention. During this waiting period, they have been requested not to attend other mindfulness or meditation activities. After the waiting period is completed (ie, 7 months after allocation), the participants in the control group will be offered the same bMBCT but without monthly follow-up sessions.

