### Outcomes

#### Primary Outcome

The primary outcome of this study is the mean difference in absolute presenteeism (measured using the WHO-HPQ) between the intervention and the waitlist control (ie, before bMBCT offered) groups at 4 weeks, 3 months, and 6 months postintervention.

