### Sample Size

The primary outcome will be analyzed using the mixed model repeated measurement (MMRM) method to compare the amount of change between groups before and after the intervention (α .05, β .10). To the best of our knowledge, no previous studies have indicated the effect size of MBPs on presenteeism among employees. The sample size was calculated based on the results of a study that showed the effect of MBPs on the quality of life (effect size=0.44) [37]. We estimated that a total of 166 participants are required; however, the sample size was set at a maximum of 220 participants, considering the dropout rate (assumed to be 25%). The dropout rate was referred to the study of an online MBP in the workplace by Aikens et al [44], which reported the dropout rate was 23%.

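### The windows at two of the three primary time points admit records that conflict with the plan's own definitions: controls after bMBCT is offered at 6 months, and mid-programme scores at week 4

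*Protocol article*

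**What the plan says.** The Protocol article's Schedule for Assessments allows ±"2 weeks from the scheduled dates for the baseline and postintervention assessments and ±4 weeks for the 3- and 6-month postintervention assessments". It attaches no further condition to either window.

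The Control Group section fixes the crossover: "After the waiting period is completed (ie, 7 months after allocation), the participants in the control group will be offered the same bMBCT".

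The Primary Outcome section compares the intervention group with "waitlist control (ie, before bMBCT offered) groups at 4 weeks, 3 months, and 6 months postintervention". The abstract gives the same three time points as a difference "between the groups at 4, 16, and 28 weeks".

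On the programme, the intervention section says that "the total number of sessions was reduced (from 8 sessions to 4 sessions"). Table 2 places one session in each of weeks 1 to 4 and the first outcome assessment in week 4. The WHO-HPQ item behind the primary outcome asks "how would you rate your overall job performance on the days you worked during the past 4 weeks".

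**The concern.** Each window is symmetric around its nominal date, and each nominal date sits close to an event that changes what the score means.

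- **6 months.** The late side of the window runs past the date on which controls become eligible for the programme. A control who answers late but within the window meets the Schedule for Assessments and fails the Primary Outcome definition. Nothing in the article says which of the two prevails. If such records enter the analysis, some controls may already have been exposed to bMBCT.
- **Week 4.** The early side of the window reaches back into the programme. A bMBCT participant who answers early has had only part of the intervention, and the recall period reaches back before it began. The article nevertheless labels the score postintervention.

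The stake is the primary comparison at these two time points. Treated controls and part-treated bMBCT participants both bring the arm means closer together. There may also be a secondary effect. Table 3 schedules no assessment of the waitlist group just before its own programme, so the 6-month reading appears to be its nearest pre-bMBCT measurement for the comparison with and without follow-up described in the Discussion.

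**Working it through.** **Inputs from the article**
- Four sessions, one in each of weeks 1 to 4 (intervention section, Table 2).
- Primary time points at weeks 4, 16 and 28 (abstract), or 4 weeks, 3 months and 6 months postintervention (Primary Outcome).
- Windows of ±2 weeks at the first outcome and ±4 weeks at 3 and 6 months (Schedule for Assessments).
- Crossover offered 7 months after allocation (Control Group).
- Recall of 4 weeks, or 28 days (WHO-HPQ).

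**Assumptions, not in the article**
- Lag from allocation to session 1: taken as 0, with 0 to 4 weeks as a range.
- Delay from the offer to a control's first session: taken as 0.
- Calendar month: 365.25 / 12 / 7 = 4.348 weeks.

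**Step 1: reproduce the plan's dates.** With 4-week months, 4 + 3 × 4 = 16 and 4 + 6 × 4 = 28, which matches the abstract exactly. With calendar months, 4 + 3 × 4.348 = 17.0 and 4 + 6 × 4.348 = 30.1.

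**Step 2: overlap at 6 months.** Overlap = (6-month date + 4 weeks + lag) − crossover date. With lag 0:

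| Reading | Window closes | Crossover | Overlap | Share of 8-week window |
|---|---|---|---|---|
| Week 28 visit, calendar 7 months | 28 + 4 = 32.0 | 7 × 4.348 = 30.4 | 1.6 weeks (11 days) | 20% |
| Calendar months throughout | 30.1 + 4 = 34.1 | 30.4 | 3.7 weeks (26 days) | 46% |
| 4-week months throughout | 28 + 4 = 32.0 | 7 × 4 = 28.0 | 4.0 weeks (28 days) | 50% |

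Each week of lag adds one week. At a 4-week lag the three overlaps are 5.6, 7.7 and 8.0 weeks. The remaining mix (calendar months for the visit, 4-week months for the crossover) would give 34.1 − 28 = 6.1 weeks at lag 0. It is left out of the range because nothing in the article suggests it.

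Each week by which a control's first session follows the offer takes one week off the overlap with actual treatment. At lag 0 that overlap disappears once the delay reaches 1.6, 3.7 or 4.0 weeks respectively.

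**Step 3: the first outcome.** The window runs from week 4 − 2 = 2 to week 4 + 2 = 6. With weekly sessions on days 0, 7, 14 and 21, a day-14 response follows two of four sessions, and the third falls that day. Of the 28 recalled days, 28 − 14 = 14 (half) precede session 1.

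**Step 4: the middle time point.** Its window is weeks 12 to 20, or 13.0 to 21.0 in calendar months. The programme ends in week 4 and the crossover is no earlier than week 28, so neither problem arises.

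**Step 5: direction and scale.** If a fraction *f* of controls answer after crossover with a share *g* of the full benefit, a standardised effect *d* becomes *d* × (1 − *f g*). The values of *f* and *g* are not in the article. As illustration only, take the planning effect of 0.44 and *g* = 0.5. Then *f* = 0.10 gives 0.44 × 0.95 = 0.418, and *f* = 0.20 gives 0.44 × 0.90 = 0.396. This would apply at the 6-month time point alone.

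**The case against.** The strongest reply is that the Primary Outcome section already excludes controls measured after the offer, and that the handling of out-of-window records belongs in an analysis plan that is not shown. In part this stands. A reader might infer that the plan intends treated controls to enter the 6-month contrast, and the document does not support that. What remains is a conflict between stated rules: the Schedule for Assessments accepts records that the Primary Outcome definition rejects, and it has no cut-off.

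A second reply is that being offered the programme is not the same as starting it. That also stands. The overlap is measured to the offer date, and a later first session would shrink the overlap with treatment. No minimum gap is stated, however, and any lag before session 1 works the other way.

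A third reply is that the label postintervention rules out a mid-programme score at week 4. The label shows the intent, but the same sentence that uses it grants the two-week early tolerance.

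Four stronger readings are tempting and should not be drawn:
- **All primary contrasts are affected.** The 3-month (16-week) time point is not.
- **An early week-4 answer is contamination.** It is incomplete exposure in the bMBCT arm; controls at that point have received nothing.
- **Baseline scores may be collected after the programme starts.** The article does not equate the scheduled baseline date with session 1, and Table 2 puts every scale in the screening period. The WHO-HPQ item is also needed for eligibility and stratification, so it must precede allocation.
- **The loss of effect can be quantified, or late controls carry the full effect.** The document gives no basis for the share of late responders or for their benefit. On the 11-day reading, about 17 of the 28 recalled days (28 − 11) would precede a control's first session, which makes full benefit implausible.

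**Conclusion.** The point holds for two of the three primary time points. On every reading of a month, the 6-month window passes the date on which controls are offered bMBCT, by about 1.6 to 4.0 weeks on the readings the text supports. This assumes no lag between allocation and session 1. It conflicts with a primary outcome that counts controls only before the offer. The first outcome window opens at about week 2, after about two of four sessions, with about half of the recall period before session 1. That does not fit a postintervention measure.

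Both would tend to shrink a true benefit. How much depends on how many participants answer at the affected edges and on when controls actually start. The document gives neither, so no size can be put on the bias. The flaw lies in window rules that the article states, so it is not a detail left to another document, and it should be corrected.

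**What to change.** Reconcile the Control Group, Primary Outcome and Schedule for Assessments sections:

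1. Close each control's 6-month window before that participant's first bMBCT session, and exclude any later record from the primary contrast. Word the Primary Outcome definition to match, so that it is clear whether the limit is the offer or the first session.
2. Open the first outcome window only after session 4, on the same dates in both arms so that timing stays comparable.
3. State every time point, window and the crossover from one origin and in one unit, and say how that origin relates to allocation and to session 1.

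This needs changes to the ePRO window settings and a short rule in the analysis plan; the treatment schedule is untouched. The cost is that a few early or late questionnaires become missing. The planned MMRM handles them by maximum likelihood without imputation, under its usual missing-at-random assumption.
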